## Abstract

**Introduction:**

Crohn’s disease (CD) is characterised by discontinuous, relapsing enteric inflammation. Instituting advanced therapies at an early stage to suppress inflammation aims to prevent future complications such as stricturing or penetrating disease, and subsequent surgical resection. Therapeutics are effective but associated with certain side-effects and relatively expensive. There is therefore an urgent need for robust methods to predict which newly diagnosed patients will develop disabling disease, to identify patients who are most likely to benefit from early, advanced therapies. We aim to determine if magnetic resonance enterography (MRE) features at diagnosis improve prediction of disabling CD within 5 years of diagnosis.

**Methods and analysis:**

We describe the protocol for a multicentre, non-randomised, single-arm, prospective study of adult patients with newly diagnosed CD. We will use patients already recruited to the METRIC study and extend their clinical follow-up, as well as a separate group of newly diagnosed patients who were not part of the METRIC trial (MRE within 3 months of diagnosis), to ensure an adequate sample size. Follow-up will extend for at least 4 years. The primary outcome is to evaluate the comparative predictive ability of prognostic models incorporating MRE severity scores (Magnetic resonance Enterography Global Score (MEGS), simplified MAgnetic Resonance Index of Activity (sMaRIA) and Lémann Index) versus models using standard characteristics alone to predict disabling CD (modified Beaugerie definition) within 5 years of new diagnosis.

**Ethics and dissemination:**

This study protocol achieved National Health Service Research Ethics Committee (NHS REC), London—Hampstead Research Ethics Committee approval (IRAS 217422). Our findings will be disseminated via conference presentations and peer-reviewed publications.

**Trial registration number:**

ISRCTN76899103.

Strengths and limitations of this studyThis is a multicentre, prospective study with a large sample size from National Health Service sites across the UK, all with established inflammatory bowel disease and magnetic resonance enterography (MRE) services.We exclusively study patients with a new diagnosis of Crohn’s disease with follow-up of at least 4 years.We evaluate the predictive ability of MRE using established scoring systems including the Magnetic resonance Enterography Global Score, simplified MAgnetic Resonance Index of Activity (sMaRIA) and the Lémann Index (LI).It is not possible to evaluate ultrasound in the present study as only static images, rather than cine loops will be available, and these will be of insufficient quality for analysis.

## Introduction

### Background and rationale

Crohn’s disease (CD) is a chronic, relapsing and remitting inflammatory disease of the gastrointestinal (GI) tract.^1 2^ Severity ranges from subtle mucosal ulceration to advanced transmural disease, which may be complicated by stricturing, fistulae and abscess.^3^ Some CD patients need regular hospital care,^4^ and 50%–80% require surgery.^5^ Imaging is crucial for diagnosis and staging because much of the small bowel (SB) is inaccessible to conventional endoscopy.^6–8^ Accordingly, at diagnosis patients with suspected CD undergo SB imaging as well as endoscopy.^9^ Magnetic resonance enterography (MRE) is increasingly used as the first-line imaging investigation in this scenario given its proven high accuracy for delineating disease distribution, severity and treatment response,^8 10–14^ while avoiding irradiation.^15 16^

Traditionally, CD treatment employs escalation of corticosteroids, immunomodulators and biological antitumour necrosis factor (TNF) in stepwise response to progressive symptoms.^6 17 18^ However, symptoms may not reflect underlying inflammation so a reactive approach risks irreversible bowel damage due to uncontrolled subclinical inflammation.^19^ The effect of tight control management on Crohn’s disease (CALM) trial demonstrated that CD treatment titrated to faecal calprotectin and blood C-reactive protein (CRP) resulted in superior bowel healing at 1 year compared with therapy based on symptoms alone.^20 21^ Accordingly, an alternative strategy that institutes advanced therapies early aims to prevent future complications such as strictures, penetrating disease, hospitalisation and surgery.

Advanced therapy usually employs biologics, such as anti-TNFα monoclonal antibodies, either alone or in combination with other immunomodulators.^2 9^ These agents are extremely effective at improving symptoms and healing bowel, but are associated with certain side-effects and are relatively expensive,.^22–24^ There is therefore a need for robust methods to identify patients who are most likely to benefit from early, advanced therapies and who will not. A systematic review and meta-analysis identified eight biomarkers displaying statistically significant prognostic potential to identify patients destined to develop severe/disabling Crohn’s disease. However, the review identified sparse primary research that evaluated cross-sectional imaging.^25^ The success of MRE as a staging and monitoring tool raises the possibility that it could also predict patient outcomes. While few series have explored a predictive role for MRE, these have not focused on newly diagnosed patients.^26 27^

Here, we describe the protocol for a non-randomised, single-arm, prospective study that aims to answer the question: ‘Do MRE features at diagnosis improve prediction of disabling CD within 5 years of diagnosis?’

### Objectives

#### Primary objective

To improve prediction of disabling CD within 5 years of diagnosis by developing and internally evaluating a multivariable prediction model comprising both existing standard predictors and those based on MRE.

#### Secondary objectives

To improve the prediction of disease phenotype within 5 years, defined by the Montreal behaviour criteria, by developing and internally evaluating a ‘baseline’ multivariable prediction model comprising standard clinicopathological variables.To identify specific combinations of individual MRE findings that best predict disabling CD within 5 years of diagnosis.To estimate the healthcare costs incurred within 5 years of a new diagnosis of CD and to explore patient, imaging and disease characteristics driving higher health economic costs.Assuming promising predictive potential, to then generate a research design for a subsequent prospective study to externally evaluate our MRE-based prediction model if appropriate.

### Study design

METRIC (Magnetic Resonance Enterography or Ultrasound In Crohn’s Disease) was a multicentre, prospective trial performed in eight National Health Service (NHS) centres across England and Scotland designed to compare the diagnostic accuracy of MRE and ultrasound (US) for the location and extent of CD.^15 28^ Consenting adult patients presenting with either newly diagnosed CD or presenting with suspected relapse were recruited: all underwent both MRE and US. Patients were followed up for 6 months minimum. In this study, we will draw solely on the group of patients who were recruited into METRIC with a new diagnosis of CD (ie, the ‘relapse cohort’ will be excluded). We will extend follow-up for the new diagnosis cohort to a minimum of 4 years.^15^ To achieve an adequate sample size, we will supplement newly diagnosed patients from METRIC (n=133) with a carefully matched retrospectively identified group of patients also newly diagnosed with CD, who did not participate in the METRIC trial.

## Methods

We adhered to the Standard Protocol Items: Recommendations for Interventional Trials reporting guidelines.^29^

### Study setting

The study will be conducted at nine UK NHS acute hospitals across England and Scotland, which participated in METRIC, supplemented by two additional NHS acute hospitals who will contribute retrospective accruals.^15 28^ One site from the METRIC trial is not included as they did not recruit any newly diagnosed patients.

### Eligibility criteria

The study will focus on newly diagnosed CD, patients either (a) enrolled in METRIC (‘METRIC cohort’) or (b) imaged using MRE as part of their routine care at diagnosis (‘retrospective cohort’) (figure 1).

**Figure 1 F1:**
[figure not shown]
Flow diagram outlining the stages of the METRIC-EF trial. BSGAR, British Society of Gastrointestinal and Abdominal Radiology; BSG, British Society of Gastroenterology; CD, Crohn’s disease; MRE, magnetic resonance enterography; METRIC, magnetic resonance enterography or ultrasound in Crohn’s disease.

#### METRIC cohort: inclusion criteria

All confirmed new diagnoses from METRIC will be eligible for the present study; inclusion criteria therefore mirror those stipulated by METRIC:

Patients aged 16 years or more.New CD diagnoses (within 3 months of time of recruitment), based on standard endoscopic, histological, clinical and radiological findings.

#### Additional retrospective cohort: inclusion criteria

The retrospective cohort will be added to METRIC accruals to achieve the required sample size.

Inclusion criteria for the retrospective cohort are as follows:

Patients aged 16 years or more with newly diagnosed CD, based on endoscopic, histological, clinical and radiological findings.MRE acquired according to METRIC standard minimum sequence data set, and performed either <3 months before or after diagnosis.Normal institutional practice is to perform MRE in all new diagnoses of CD.At least 4 years clinical follow-up data available.

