#### Exclusion criteria

Exclusion criteria for METRIC (and so carried forward) are as follows:

Any psychiatric or other disorder likely to impact on informed consent.Evidence of severe comorbidities which makes it undesirable for the patient to participate in the study.Pregnancy.Contraindication to MRI (eg, cardiac pacemaker, severe claustrophobia and inability to lie flat).Final diagnosis other than CD.Enrolled in the METRIC study but not part of the final new diagnosis cohort.

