##### Simplified Magnetic Resonance Index of Activity (sMaRIA)

The simplified MAgnetic Resonance Index of Activity (sMaRIA) has been validated against endoscopic reference standards, and is used increasingly to assess treatment response in clinical trials^8 10–12 33^ (table 3).

**Table 3 T3:** Derivation of the simplified MAgnetic Resonance Index of Activity (sMaRIA)

Feature	Description
Mural thickness	Binary: measured in mm using software callipers, scored as abnormal if >3 mm
Mural oedema	Binary: present if there is high signal intensity on T2 sequences with fat saturation, compared with normal-appearing loops
Fat stranding	Binary: present if there is loss of the normal sharp interface between the intestinal wall and mesentery, with oedema/fluid in the perienteric fat
Ulceration	Binary: present if mucosal surface has a deep depression, visible on 2 MRI sequences
sMaRIA score for that segment	=1 point for each of mural thickness, mural oedema and fat stranding; 2 points for ulceration (maximum 5 points per segment)

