##### Lémann Index (LI)

The LI^34^ (table 4) is based on comprehensive assessment of structural bowel damage, including stricturing, penetrating lesions (ﬁstulae and abscesses) and surgical resection, and is applicable to different settings, such as early or advanced disease, patients with or without surgery, or with different CD locations and extension. The score comprises several factors that can be assessed either clinically, or using imaging or via endoscopy. We will use the imaging-derived score. Since the anal canal will not have been imaged specifically for METRIC, we will omit this score.

**Table 4 T4:** Derivation of the Lémann Index

Organ	Method of assessment	N*	Segment	Grade 1	Grade 2	Grade 3
Surgical interventions†						
Upper tract	History	3	Oesophagus, stomach, duodenum	–	Bypass diversion or stricturoplasty	Resection
Small bowel	History	20	Each 20 cm SB segment	–	Bypass diversion or stricturoplasty	Resection
Colon/rectum	History	6	Each colonic segment	–	Stoma, bypass diversion or stricturoplasty	Resection
Stricturing lesions						
Upper tract	MRI	2	Stomach, duodenum	Wall <3 mm; segmental enhancement without prestenotic dilatation	Wall thickening ≥3 mm or mural stratification with no prestenotic dilatation	Stricture with prestenotic dilatation
Small bowel	MRI	20	Each 20 cm SB segment	Wall <3 mm; segmental enhancement without prestenotic dilatation	Wall thickening ≥3 mm or mural stratification with no prestenotic dilatation	Stricture with prestenotic dilatation
Colon/rectum	MRI	6	Each colonic segment	Wall <3 mm; segmental enhancement without prestenotic dilatation	Wall thickening ≥3 mm or mural stratification with no prestenotic dilatation	Stricture with prestenotic dilatation or >50% of the lumen
Penetrating lesions						
Upper tract	MRI	2	Stomach, duodenum	–	Deep transmural ulceration	Phlegmon or fistula
Small bowel	MRI	20	Each 20 cm SB segment	–	Deep transmural ulceration	Phlegmon or fistula
Colon/rectum	MRI	6	Each colonic segment	–	Transmural ulceration	Phlegmon or fistula

*n is the number of segments within a particular organ.

†This information will be collated from the original METRIC records, although a relevant surgical history will be very rare since included patients are, by definition, those with a new diagnosis of Crohn’s disease.

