### Statistical methods—outcomes

#### Primary outcome

Comparative predictive ability of prognostic models incorporating MRE severity scores (MEGS, sMaRIA and Lémann index) versus models using standard characteristics alone to predict disabling CD (modified Beaugerie definition) within 5 years of new diagnosis

We will develop a multivariable prognostic model using prespecified standard predictors (age at recruitment as new diagnosis, smoking, gender, disease status at diagnosis (stricturing disease, perianal disease, severe endoscopic disease, location of disease as L1/L2/L3/L4, initial need for steroid therapy, weight loss of at least 5 kg, CRP, white cell count, faecal calprotectin, haemoglobin and platelets). Continuous variables will be retained where possible, with transformations and polynomial transformations when needed. Categorised variables will be retained as prespecified in clinical report form except where modelling requires combination of categories with small numbers. Missing covariates will be handled via multiple imputation, under the ‘missing at random’ assumption.^44^ We will compare the additive effect on model fit of each MRI score (MEGS, sMaRIA and LI as PCA variables) to the baseline standard model as a linear offset. An increase in model performance will be based on an improvement in the number of patients correctly classified for disabling disease, using models including MRE compared with a standard model. Model performance will be measured using sensitivity, specificity and net benefit. We will also assess difference in model fit using Bayesian Information Criteria (BIC) and we will report c-index for each model. Internal validation using bootstrap samples (sampling with replacement) will use at least 200 or more bootstrap samples until estimates remain stable. Model prediction at 1-year, 2-year and 3-year time horizons will also be reported.

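### Baseline MRE may follow treatment or even an outcome event, because retrospective scans up to 3 months after diagnosis are allowed and outcomes are counted from diagnosis

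*Protocol article*

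**What the plan says.** - **Question.** The Protocol article (Background and rationale) asks: "Do MRE features at diagnosis improve prediction of disabling CD within 5 years of diagnosis".
- **Retrospective cohort.** The MRE may be "performed either <3 months before or after diagnosis". The abstract gives the same window without direction: "MRE within 3 months of diagnosis".
- **METRIC cohort.** The criterion is "New CD diagnoses (within 3 months of time of recruitment". It links diagnosis to recruitment; the article gives no interval between diagnosis and MRE for this cohort.
- **Exclusions.** None of those listed concerns treatment or surgery before the scan.
- **Outcome.** The primary definition counts hospitalisation after diagnosis and any intestinal resection over 50 cm, on a 5-year horizon that starts at diagnosis.
- **Scores.** sMaRIA is described as "used increasingly to assess treatment response in clinical trials". The Lémann Index scores resection, and its table footnote expects that "a relevant surgical history will be very rare since included patients are, by definition, those with a new diagnosis of Crohn’s disease".
- **Baseline model.** It includes "initial need for steroid therapy", with no timing relative to the scan.

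**The concern.** A prognostic predictor should be measured before the outcome can occur, and in the state in which it will be used. Here a patient diagnosed in week 0, treated from week 1 and scanned in week 10 is eligible in the retrospective cohort. So is one admitted or operated on in week 3 and scanned in week 10.

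These two cases push the result in opposite directions. Treatment before the scan lowers activity scores, probably more often in patients who began with worse disease, and weakens the link between score and outcome. An event before the scan lets the scan reflect the outcome it is meant to predict. The Lémann Index shows this most plainly, since one operation can raise the predictor and also meet the outcome definition. The primary outcome is the added value of these scores over the standard model, so both errors fall on the quantity of interest.

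**Working it through.** **1. The plan's own figures.** 207 × 0.55 = 113.9 and 207 × 0.60 = 124.2 events; 207 × 0.40 = 82.8 and 207 × 0.45 = 93.2 non-events. These match the stated 114–124 and 83–93. The cohort targets add up: 131 + 76 = 207. None of these figures depends on scan timing, so none changes.

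**2. How many events could precede a scan?** The Assumptions section gives 57% at 5 years from the literature and 16% at 1 year from a local audit, and takes development as roughly linear. Over 3 months:
- 57% × 3/60 = 2.9%; 16% × 3/12 = 4.0%.
- Retrospective cohort, if every scan were at the 3-month limit: 76 × 0.029 = 2.2 to 76 × 0.040 = 3.0 patients.
- All 207, if METRIC scans were equally late (not stated): 207 × 0.029 = 6.0 to 207 × 0.040 = 8.3 patients.

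Real scans will mostly be earlier, which lowers these counts. Admissions clustered soon after diagnosis would raise them.

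**3. Inflation from events before the scan (assumed inputs).** Take one score with a true c-index of 0.70, normal within outcome groups: d = √2 × Φ⁻¹(0.70) = 0.742. If a share q of patients with the outcome have their score raised by 0.5 SD, then

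c = (1 − q) × 0.70 + q × Φ((0.742 + 0.5)/√2) = 0.70 + 0.110q.

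- q = 0.14, 0.35, 0.52, 0.70 gives 0.715, 0.738, 0.757, 0.777, which agrees with simulation of 400,000 subjects. These shares are far above those in step 2.
- With step 2's upper count, q = 8.3/119 = 0.07 (119 = 207 × 0.575), and c = 0.708.

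**4. Attenuation from treatment before the scan (assumed inputs).**
- Odds-ratio scale: half need steroids, more often those with higher activity; 25–50% of these are scanned after starting (12.5–25% of all patients); treatment lowers the score by 0.5–1.0 SD. A true odds ratio per SD of 1.5 is estimated as 1.42–1.49, and 2.0 as 1.80–1.97. The likelihood-ratio evidence falls by about 3–14%. With steroid need in the model, a similar simulation gave 1.43–1.48 for 1.5 and a loss of about 3–13%.
- c-index scale, true value 0.70, base share f = 10%, 25%, 37% (76/207), 50%:

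| Affected scans | 10% | 25% | 37% | 50% |
|---|---|---|---|---|
| Half the correlation kept | 0.690 | 0.675 | 0.663 | 0.650 |
| No information | 0.680 | 0.650 | 0.627 | 0.600 |
| Lowered 0.5 SD, in 1.4f of patients with the outcome and 0.6f of those without | 0.688 | 0.671 | 0.659 | 0.645 |

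**5. Against sampling error.** For a standardised score the standard error of the log odds ratio is at least about 1/√(207 × 0.575 × 0.425) = 0.14; take 0.15. The largest shifts are ln(1.5/1.42) = 0.055, about 0.4 standard errors, and ln(2.0/1.80) = 0.105, about 0.7 standard errors.

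Steps 3 and 4 mostly describe a score on its own. The study's comparison is the gain over a standard model, whose sensitivity to timing cannot be worked out from the article.

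**The case against.** **Different windows.** A reader might infer that the cohorts have different MRE windows, or that a METRIC scan can fall more than 3 months after diagnosis. The article does not support this. Its METRIC criterion concerns recruitment, and the METRIC protocol, which may fix scan timing, is not shown. Imposing a new METRIC window is therefore not justified.

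**Treated bowel as fact.** Nor does the article show that scans were made on treated bowel. The introduction places small-bowel imaging in the diagnostic work-up, and the retrospective criteria require sites that routinely perform MRE in new diagnoses. Many scans will precede treatment. Only a possibility can be claimed.

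**Dilution only.** A reader might also infer that the MRE effect must be diluted. Events before the scan work the other way, so the direction is open.

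**Resection.** Prior surgery is expected to be very rare. A rise in the Lémann Index after resection is what that index is built to show, so divergence of the three scores is not itself a fault. The footnote, however, reasons from the diagnosis being new, which does not cover surgery at or just after diagnosis. It also names METRIC records as the source, which patients outside METRIC do not have.

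**Steroid need is modelled.** This carries part of the severity signal but does not separate treatment before the scan from treatment after it.

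**Routine use.** A model for practice may reasonably use MRE as obtained around diagnosis. That argues against a treatment indicator in the main models; it does not justify counting events that precede the predictor.

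**An unseen analysis plan** may hold sensitivity analyses. Eligibility and the start of the outcome period are nevertheless fixed in this article.

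**Conclusion.** The point stands as a gap in temporal order. The stated criteria allow a baseline MRE to follow treatment, a qualifying hospitalisation or a resection, and a resection over 50 cm before the scan would enter both the Lémann Index and the outcome. The bias in the added value of MRE may go either way.

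Its size is probably modest. The protocol's event rates imply about 2 to 3 retrospective patients with an event before the scan even if all were scanned at the limit, and 6 to 8 if the whole sample were. The assumed treatment scenarios on the odds-ratio scale move the log odds ratio by at most about 0.7 standard errors. These sizes rest on assumed shares, assumed treatment effects and roughly linear event accrual; the documents supply only the event rates and sample size. Larger c-index shifts, such as 0.70 to 0.60 or to 0.78, need shares that nothing in the article supports. The expected event counts are unaffected. The change is worth making because it is cheap, not because the study is at serious risk.

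**What to change.** 1. For each patient, use the dates of MRE, diagnosis, first steroid, immunomodulator or biologic, any resection, and the endpoint.
2. Exclude from the prediction set patients whose resection or other qualifying outcome event precedes the baseline MRE. Alternatively, count outcomes only from the later of diagnosis and MRE. State the choice before modelling.
3. Report scan-to-diagnosis and scan-to-treatment intervals by cohort.
4. Add a sensitivity analysis of the primary comparison, either restricted to MREs done before treatment or adjusted for treatment started before MRE. Leave the main models as planned.

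**Cost.** The consensus panels already record the endpoint date, and the health-economic form already covers imaging, surgery and medication. Some date abstraction remains, including a source for surgical history outside METRIC. On the rates above, exclusion would remove a few patients, and the restricted analysis will be less precise. No eligibility rule for completed METRIC scans needs to change.
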